## Abstract

**Introduction:**

Children’s early development is affected by caregiving experiences, with lifelong health and well-being implications. Governments and civil societies need population-based measures to monitor children’s early development and ensure that children receive the care needed to thrive. To this end, the WHO developed the Global Scales for Early Development (GSED) to measure children’s early development up to 3 years of age. The GSED includes three measures for population and programmatic level measurement: (1) short form (SF) (caregiver report), (2) long form (LF) (direct administration) and (3) psychosocial form (PF) (caregiver report). The primary aim of this protocol is to validate the GSED SF and LF. Secondary aims are to create preliminary reference scores for the GSED SF and LF, validate an adaptive testing algorithm and assess the feasibility and preliminary validity of the GSED PF.

**Methods and analysis:**

We will conduct the validation in seven countries (Bangladesh, Brazil, Côte d’Ivoire, Pakistan, The Netherlands, People's Republic of China, United Republic of Tanzania), varying in geography, language, culture and income through a 1-year prospective design, combining cross-sectional and longitudinal methods with 1248 children per site, stratified by age and sex. The GSED generates an innovative common metric (Developmental Score: D-score) using the Rasch model and a Development for Age Z-score (DAZ). We will evaluate six psychometric properties of the GSED SF and LF: concurrent validity, predictive validity at 6 months, convergent and discriminant validity, and test–retest and inter-rater reliability. We will evaluate measurement invariance by comparing differential item functioning and differential test functioning across sites.

**Ethics and dissemination:**

This study has received ethical approval from the WHO (protocol GSED validation 004583 20.04.2020) and approval in each site. Study results will be disseminated through webinars and publications from WHO, international organisations, academic journals and conference proceedings.

**Registration details:**

Open Science Framework https://osf.io/ on 19 November 2021 (DOI 10.17605/OSF.IO/KX5T7; identifier: osf-registrations-kx5t7-v1).

Strengths and limitations of this studyThe study collects validation data (n=8736 children) for the Global Scales for Early Development (GSED) in seven countries that vary in geographic, linguistic, cultural and sociodemographic characteristics.The methods for the validation of GSED are systematic across sites and follow rigorous standard operating procedures based on the best scientific evidence available.A tablet-based App is used for data collection to make the administration of the GSED measures user-friendly, to reduce recording and transcribing errors and to facilitate adaptive testing.The GSED short form and long form aim to include items that are culturally neutral and fit the Rasch model, which assume that child development milestones are age-ordinal, to create D-scores while psychosocial items are included in a separate measure (GSED psychosocial form (PF)) and cultural-specific items can be supplemented by countries.The three secondary aims (preliminary reference scores, an adaptive testing algorithm and the feasibility and validity of the GSED PF) are exploratory and will require further research.

## Introduction

Prenatal and early postnatal experiences have significant impacts on early childhood development (ECD) and can influence the accrual of health, well-being and productivity throughout the life course.^1^ To promote current and sustainable peace and prosperity, the United Nations has focused the Sustainable Development Goals (SDGs) on improving children’s outcomes in the early years through multiple targets. The most explicit target for young children is SDG 4 (Education goal), which requires reporting on the ‘proportion of children under 5 years of age who are developmentally on track in health, learning and psychosocial well-being, by sex’.^2^

There are few valid measures that can be used globally to assess child development for children under 3 years of age. Current measures of ECD range from proxy measures (eg, prevalence of country-level stunting and poverty) to detailed measures of individual performance on developmental tasks.^3^ The Early Childhood Development Index 2030 (ECDI 2030)^4^ does not include children below 2 years of age. A recent review has identified the creation and validation of population-based instruments for assessing very young children as a global priority.^5^

The Global Scales for Early Development (GSED) build on advances made by analyses of existing global datasets,^6^ and new data collection^7^ that demonstrated the cross cultural applicability of items that measure young children’s development. Three research teams^8^ joined efforts to develop the GSED in response to the pressing need for instruments and metrics to measure ECD at population and programmatic levels across diverse parts of the world.

### The GSED

The GSED consist of three open-access measures developed by a WHO-led team to provide a standardized methodology for measuring the development of children aged 0-3 years (0-36 months) across diverse cultures and contexts.^9 10^ They were developed for two objectives: 1) for population-level evaluation and 2) for programmatic evaluation through the caregiver report GSED Short Form (SF) and/or directly administered Long Form (LF). Additionally, a caregiver report GSED psychosocial form (PF) was created for measuring psychosocial behaviours. The development and piloting of the GSED SF, LF and PF are described elsewhere.^9–11^

The GSED SF and LF produce metrics on the same age-ordinal scale and quantify the same latent construct. The Developmental Score (D-score) (see box 1) underlies both measures and reflects children’s overall development across multiple domains typically demonstrated in this age group (eg, cognitive, motor, language, social-emotional).^6^ The GSED PF items, designed to measure non-normative developmental patterns, including behavioural or regulatory challenges, are not age-ordinal and do not use the D-score metric.

Box 1The Developmental Score (D-score)The Developmental Score,^15^ or D-score, is a unidimensional latent variable measuring child development during the first 3 years across multiple domains. The milestones that make up the D-score conform to the Rasch model,^28^ thus yielding a scale with interval properties with a fixed unit (figure 1). It is therefore possible to calculate a meaningful difference between two D-scores. Similar to height-for-age Z-score, given suitable age-conditional references, the D-score can be transformed to a Z-score that accounts for children’s age (ie, Development for Age Z-score, or DAZ). The DAZ facilitates comparisons across children of different ages.

**Figure 1 F2:**
[figure not shown]
Development chart. Reproduced with permission from Van Buuren and Eekhout.^15^

## Aims

The primary aim of this study is to validate the GSED measures,^11^ through testing for measurement invariance and evaluation of the psychometric properties to measure development among children under 3 years (<36 months) globally (including creation of D-scores and Development for Age Z-score (DAZ)).

Specific objectives:

Fit a Rasch model to the item data to calculate the D-scores and DAZ.Investigate differential item functioning (DIF) and differential test functioning (DTF) across sites to determine measurement invariance.Examine psychometric properties of the GSED SF and LF:Test–retest and inter-rater reliability (score and item level).Concurrent validity (association between scores on GSED and Bayley Scales of Infant and Toddler Development (Bayley-III) or Griffiths Scales of Child Development administered concurrently).^12^Convergent validity (strength of association between GSED D-scores and other theoretically relevant constructs).Predictive validity (association between GSED scores 6 months after initial assessment).

The secondary aims are to: (1) establish preliminary reference scores (The population has not been selected as a representative sample of all children aged <3 years in each site (as would happen in a countrywide population census). Selection and recruitment of a representative sample was beyond the scope of this study and not required for validation purposes. We are therefore developing ‘reference scores’ which should not be interpreted as population-sampled norms.) for optimal development on the D-score (GSED SF and LF), (2) develop and validate an adaptive testing algorithm and (3) obtain preliminary validity data on the psychometric properties of the GSED PF.

## Methods

### Design and study sites

The GSED validation study uses a prospective cross-sectional design with a longitudinal component of age and sex stratified samples of children in seven countries. The countries are culturally, linguistically and geographically diverse, representing low-income (Bangladesh, Côte d’Ivoire, Pakistan, United Republic of Tanzania), middle-income (Brazil and The Republic of China) and high-income (The Netherlands) settings. Samples in each site are not nationally representative; however, they are diverse, for example, covering both rural/urban settings.

Preparation and feasibility phases are described elsewhere,^11^ and assess feasibility of administration of GSED and associated measures including processes for translating and culturally adapting GSED and other study measures, creating data management systems and training teams in data collection procedures.

### Patient and public involvement

Caregivers of children 0–41 month-olds were involved in the study design as the burden of the assessment was discussed with them in a pilot stage through qualitative data collection. We intend to disseminate the main results to trial participants and will seek patient and public involvement in the development of an appropriate method of dissemination.

### Study sample

The study sample includes children between 0 and 41 months of age (inclusive) living in study areas (see table 1 for inclusion and exclusion criteria). The small sample of children from 36 to 41 months aims to ensure that parameters are estimated with adequate precision for children at the top of our age range (36 months).

**Table 1 T1:** Study sample inclusion and exclusion criteria

Sample	Inclusion criteria	Exclusion criteria
Total per site n=1248 (as described in sample size section below)	Age 0–41 months Family speaks to the child in same language as GSED translation Primary caregiver available to participate	Missing gestational age (ultrasound or last menstrual period (LMP)) Missing birth weight data Acutely unwell at time of assessment (temporary exclusion: to be rescheduled after 7 days)

GSED, Global Scales for Early Development.

#### Recruitment and consent

In each site, the sampling frame consists of a list of potentially eligible caregiver–child dyads residing in the defined study area. Lists of potential participants are created in compliance with ethical review boards approved processes; they vary by site and may include: participants in local pregnancy surveillance systems, families who have previously agreed to be contacted for participation, from hospital/health centre registries or families with children attending local child health/care centres. Sites using registries will rely on hospital or health centre staff (unaffiliated with GSED) to contact families and obtain consent for sharing their information with the GSED team. A sample listing of the pre-consented families will be provided to the GSDE team for recruitment. Sites recruiting families from local child health/care centres will rely on advertisements or flyers with information about the project, participation requirements, GSED team contact information for questions, and a scan code or website link for interested families to provide basic eligibility information and consent to be contacted for enrolment.

Eligible children are sampled from this list using the GSED sampling scheme (figure 2). To minimise clustering of correlated scores within households, one child per caregiver and in multi-family household is selected, guided by age and sex quotas. For siblings or twins, one is chosen randomly. Target children’s primary caregiver (person most familiar with the child and spends most time with them) is approached for consent and enrolment. A non-technically worded information sheet is shared and consent to participate is obtained at first visit. In the Netherlands, participants provide consent online, confirmed by study staff at first visit. Refusals to participate and dropouts are registered and replaced.

**Figure 2 F1:**
[figure not shown]
Study sampling schema diagram. ECDI, Early Childhood Development Index; GSED, Global Scales for Early Development.

#### Sampling frame and schemes

Sample size for recruitment within each site is 1248 children (total 8736 children) across seven countries. After consent is provided, children are allocated by sex and age groups using a randomization procedure to one of several sampling schema (eg, predictive, reference-score, reliability; figure 2). See sampling in online supplemental table S1 for sampling frame. Out of the full site sample of 1248 children, 504 children per site are randomly selected for re-evaluation 6 months later to assess predictive validity (primary aim). A second scheme indicates the minimum subsample of children needed to calculate preliminary reference scores (secondary aim) that will facilitate cross-country comparisons. To maximise precision of parameter estimates, larger quotas are kept for the youngest age brackets where rates of development are accelerated. A third scheme addresses inter-rater reliability for 90 children per site using two assessors who independently assess the same child sequentially or within 24 hours^12^ (We note that this procedure differs from typical inter-rater reliability (IRR) designs which involve simultaneous scoring of a single assessment. This sequential design was necessitated by logistical constraints. Given that this design captures both variance due to differences in raters and differences in occasions, the observed IRR represents a lower bound for the true inter-rater reliability of the assessments.). Test–retest (intra-rater reliability) is performed by inviting 50 children per site to return for repeat assessment with the same rater within 7–10 days. For concurrent validity, to assess the GSED against the Bayley-III, a sample size of n=150 per country produces a two-sided 95% CI 0.15 to 0.44, when the estimate of Pearson’s product-moment correlation is 0.3, with an equal spread of participants tested across age and sex.

10.1136/bmjopen-2022-062562.supp1Supplementary data

In the Netherlands, the GSED SF and PF are administered online. A subset of participants (n=32) are interviewed face-to-face to compare method of administration. To determine test–retest reliability (intra-rater reliability), the primary caregiver completes the SF and PS form online and then a second time 7–10 days later.

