#### Training and quality control

Training of local master trainers is performed by the WHO team for the GSED SF, PF and LF, using slide presentations, discussion forums, audio–visual aids and practice exercises. Local master trainers are responsible for training local field teams using materials adapted and translated to local languages. Reliable administration of the GSED measures must be met (inter-rater agreement with a master trainer of ≥90%) for certification.

To ensure quality assurance, 10% of all the study visits are observed by the study supervisor in person (or through video-recording in the Netherlands), covering each child age band and certified assessors. Supervisors independently complete questionnaires being administered by the assessor and complete a fidelity checklist. Assessors are given feedback based on checklist score. Supervisors review quality assurance findings with the WHO biweekly, along with discussions with the subject matter experts for further resolution, as needed.

The GSED application software for data collection has built-in data range and consistency checks. Data managers review and resolve issues daily in consultation with the local field team and/or WHO team.

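### Inter-rater reliability rests on 90 sequential pairs per site, a lower bound of unknown looseness, while simultaneous supervisor-assessor scoring on 10% of visits is left out of the stated reliability analysis

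*Protocol article*

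**What the plan says.** Under *Sampling frame and schemes* the article sets the design: "A third scheme addresses inter-rater reliability for 90 children per site using two assessors who independently assess the same child sequentially or within 24 hours". It acknowledges that "this procedure differs from typical inter-rater reliability (IRR) designs which involve simultaneous scoring of a single assessment", and explains: "This sequential design was necessitated by logistical constraints". Because "this design captures both variance due to differences in raters and differences in occasions", it concludes that "the observed IRR represents a lower bound for the true inter-rater reliability of the assessments".

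Under *Training and quality control*, "10% of all the study visits are observed by the study supervisor in person" (by video recording in the Netherlands), spread over age bands and certified assessors. There, "Supervisors independently complete questionnaires being administered by the assessor and complete a fidelity checklist". The uses named are feedback to assessors and a biweekly review with WHO.

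Under *Statistical analysis*, inter-rater and test–retest reliability are analysed with the ICC at score level and Gwet's AC1 at item level, with 95% CIs. Items at 0.4 or above count as adequately reliable, and those between 0.4 and 0.5 are discussed for modification. The supervisor-assessor pairs are not mentioned.

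**The concern.** By the article's own definition, the quality-control co-scoring is the usual inter-rater design: two people independently score one administration. The logistical reason for doing without it fits poorly with a section that provides for it on a tenth of all visits.

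Inter-rater reliability at score and item level is a specific objective under the primary aim, and the final item sets are to be chosen from the validation analyses. The sequential pairs give one coefficient in which rater disagreement and change in the child's or caregiver's response cannot be told apart. A low item value could mean that assessors score differently, or only that the child did something different the second time. The first calls for a change to the item or the training; the second does not. The test–retest sample (50 per site, same rater, 7–10 days apart) does not separate the two, because its interval is much longer than the 24 hours or less of the inter-rater scheme.

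**Working it through.** **The plan's own figure.** No target ICC, precision or power is given for the 90 per site, so that number cannot be reproduced. Neighbouring figures do reproduce: 7 × 1248 = 8736, and a Fisher z interval for r = 0.3 with n = 150 gives 0.147 to 0.439, matching the stated 0.15 to 0.44.

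**How many co-scored visits there are.** Inputs from the article: 1248 children per site, 504 re-evaluated at 6 months, one to three visits depending on site, 10% of visits observed.

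| Assumption | Co-scored visits per site |
|---|---|
| One visit per child | 0.10 × 1248 = 124.8 |
| One visit plus one follow-up visit for 504 | 0.10 × (1248 + 504) = 175.2 |
| Three visits per child | 0.10 × 3 × 1248 = 374.4 |
| Three visits plus follow-up | 0.10 × (3 × 1248 + 504) = 424.8 |

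Over seven sites the first row gives 7 × 124.8 = 873.6, against 7 × 90 = 630 sequential pairs if all sites run that scheme. These are visits, not forms. Where forms fall on different visits, the count per form is lower than the visit count: 374.4 visits spread evenly over three visit types would be 124.8 of each. The article gives no share per form.

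**What the extra number buys in precision.** With the approximation SE = 1/√(n − 1.5) on the Fisher z scale, an ICC of 0.80 has a 95% CI of 0.712 to 0.864 at n = 90 and 0.727 to 0.855 at n = 125. The gain is small. The value of the co-scored pairs lies in what they measure, not in how many there are.

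**Is the lower-bound statement right?** Let C, R, O and E be child, rater, occasion and residual variance.

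- Sequential ICC = C / (C + R + O + E)
- Simultaneous ICC = (C + O) / (C + O + R + E)

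The denominators are equal and O ≥ 0, so the sequential value cannot exceed the simultaneous one. Against the article's own benchmark the statement holds.

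**How loose can the bound be?** The article gives no variance components. Assume C = 1, R = 0.03, E = 0.07 and vary O:

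| O | Sequential ICC | Simultaneous ICC |
|---|---|---|
| 0 | 0.909 | 0.909 |
| 0.05 | 0.870 | 0.913 |
| 0.10 | 0.833 | 0.917 |
| 0.20 | 0.769 | 0.923 |
| 0.30 | 0.714 | 0.929 |

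Rater variance is the same in every row, yet the sequential coefficient moves by about 0.2. Sequential data alone cannot say which row applies.

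**Effect on the item rule.** Assume 50% prevalence, so that AC1 = (agreement − 0.5)/0.5. Let d be the raters' disagreement on the same response and f the share of responses that change between occasions. Co-scored agreement is 1 − d; sequential agreement is (1 − d)(1 − f) + d·f.

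| d | f | Co-scored AC1 | Sequential agreement | Sequential AC1 |
|---|---|---|---|---|
| 0.10 | 0.10 | 0.80 | 0.82 | 0.64 |
| 0.10 | 0.20 | 0.80 | 0.74 | 0.48 |
| 0.10 | 0.25 | 0.80 | 0.70 | 0.40 |
| 0.15 | 0.25 | 0.70 | 0.675 | 0.35 |

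Items that raters score well can thus fall into the 0.4–0.5 band or below 0.4 through occasion variation.

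**The case against.** The strongest reply is that the limitation is disclosed. The article says the design is atypical, gives the reason, names the mixed variance and states the direction of the bias. A rater-plus-occasion coefficient is interpretable and conservative. That stands: nothing is concealed and the sequential estimate is not wrong.

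The co-scored pairs also have real limits. Only one person administers, so differences in how assessors elicit behaviour are left out and the estimate tends to be too high. On the short form (SF), assessors record the caregiver's answer whatever they observe themselves, so two listeners will agree almost perfectly. The text speaks of questionnaires, which leaves coverage of the directly observed LF open. The second rater is a supervisor, and assessors know they are watched and receive feedback. All of this stands and governs how the result should be labelled.

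That the pairs go unused is inferred from the sections shown. The supplement and full protocol are not available and might include them.

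Two stronger readings are tempting, and the document supports neither:

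- *That the lower bound is not assured, because caregivers remember answers and children practise tasks within 24 hours.* Under co-scoring the caregiver answers once, so recall can only raise sequential agreement towards the co-scored value. Practice makes the second performance differ, which lowers agreement. Neither reverses the inequality above.
- *That the gap between the two estimates is the occasion variance.* It also contains administration and elicitation differences, supervisor-versus-assessor differences and the effect of being observed.

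**Conclusion.** The point holds as a case for a specific added analysis, not as an error in the sequential design. The article's reason for lacking simultaneous scoring does not fit its own quality-control procedure, and the stated reliability analysis leaves out double scores that the plan already generates: about 125 visits per site at one visit per child, with the count per form to be established. The lower-bound statement should stay. What is missing is an indication of how loose it is. Under the assumed inputs, the ICC could be understated by up to about 0.2 (0.714 against 0.929), and an item with co-scored AC1 of 0.80 could appear at 0.48 or 0.40. Those sizes rest on assumed variance components, 50% prevalence and assumed rates of response change. The practical gain is mainly for the LF and depends on the LF being co-scored. For the SF completed online in the Netherlands there are no such pairs.

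**What to change.** Add to *Statistical analysis* the ICC (score level) and Gwet's AC1 (item level), with 95% CIs, from the co-scored quality-control visits, per form and site where pairs exist. Report them beside the sequential estimates and label them scoring agreement. The sequential figure is the lower bound and the co-scored figure tends to an upper bound, so together they bracket inter-rater reliability. Apply the 0.4 cut-off and the 0.4–0.5 discussion band with both in view, so that no item is flagged for occasion variation alone. Keep the lower-bound sentence, and state that the gap is not pure occasion variance. State also which forms supervisors co-score, in particular whether the LF is included, and how many pairs each form yields.

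The cost is export and analysis of scores that supervisors already complete, provided that their item responses are stored in analysable form, which the article does not say. No extra visits are needed. The report should name the downsides: supervisor rather than peer raters, assessors who know they are observed, near-ceiling SF agreement, and no pairs for the Dutch online SF.
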